## Abstract

**Background:**

Frailty is a dynamic and reversible clinical syndrome in older adults that profoundly affects an individual’s quality of life, health outcomes, and overall prognosis, thereby underscoring the importance of early identification and timely intervention. Alterations in the biomechanical parameters of lower limb muscles may constitute the pathophysiological underpinnings of frailty. Surface electromyography (sEMG) is a vital tool for assessing neuromuscular function. To date, there are no reports on the characteristics of surface electromyographic in the lower limbs of frail older individuals.

**Methods:**

This is an observational category matching case-control study. We aim to recruit 75 frail older adults and 75 matched non-frail older participants (1:1), to be assigned respectively to the case and control groups. All subjects will undergo sEMG of the lower limb muscles during a 10-meter walk test and will be assessed for gait and balance. The primary outcome will be the difference in sEMG parameters between the two groups, including root mean square (RMS), integrated electromyography (IEMG), averaged electromyography (AEMG), mean power frequency (MPF), and median frequency (MF), as well as those computed from these metrics, including symmetry index (SI), muscle activation sequences, and muscle contribution rates. Secondary outcomes will encompass the time taken to complete the 10-meter walk test and assessments of gait and balance. Furthermore, the relationship between electromyographic parameters and the state of frailty will be evaluated, and the predictive capability of these sEMG parameters for identifying frailty will be explored.

**Trial registration number:**

ChiCTR2300078953

## Introduction

As global aging dynamics intensify, frailty has emerged as a major challenge to healthy aging. Frailty is a clinical syndrome of increased vulnerability and dysfunction due to the cumulative decline of multiple body systems, characterized by unconscious weight loss, reduced grip strength, slowed gait, decreased physical activity and self-reported fatigue, which significantly increases the risk of adverse health outcomes such as falls, disability and death [1–3], and imposes a serious economic burden on the families of patients, making social security for old-age and health care more challenging [1,4,5]. However, the process of frailty can be delayed and reversed, and effective interventions can prevent the occurrence of adverse events in older adults in the pre-frailty stage and delay the entry into the frailty stage, or even recover from the pre-frailty stage to a non-frailty state [1,6], so early screening and identification of high-risk groups is an important part of the optimal management of frailty in older adults.

Slowed gait speed is a component of the frailty phenotype, and studies have shown significant decreases in gait speed in frail older adults, whether they are walking at habitual speeds or walking at fast speeds [7–9]. While gait speed can predict frailty and some adverse health outcomes [10–12], numerous factors in daily life can slow walking speed in older adults, making it a less effective predictor when considered in isolation. Decrements in walking ability may be related to reductions in muscle mass, muscle contractility, balance, and other physiological factors [13–15], with decreased strength and endurance in lower limb muscles strongly correlated with heightened frailty risk [16]. Notably, the rectus femoris, semitendinosus, tibialis anterior, and medial head of gastrocnemius are critical to walking; reductions in their strength may be pivotal to the observed deceleration in gait speed [17,18]. These observations suggest that changes in the biomechanical parameters of lower limb muscles could underpin the pathophysiology of frailty, and identifying these characteristic changes is crucial for developing effective frailty screening, prevention, and rehabilitation programs.

Among the various methods used to assess muscle behavior, electromyography (EMG) is regarded as the ‘gold standard’. Surface electromyography (sEMG), a crucial tool for neuromuscular function research, provides real-time, objective, non-invasive, and dynamically sensitive measurements. It allows for precise monitoring of muscle activities by recording bioelectrical signals from muscles during activity, accurately reflecting changes in muscle activation patterns, fatigue levels, muscle strength, muscle contribution rates, and muscle coordination [19,20]. Although widely used in sports science, sports medicine, and rehabilitation [19,21], there is yet to be research linking sEMG with frailty in older adults.

### Primary and secondary objectives

The primary objective of this study is to compare the surface electromyography (sEMG) signal parameters of the rectus femoris, semitendinosus, tibialis anterior, and medial head of the gastrocnemius muscles in both lower extremities during a 10-meter walk test between frail and non-frail older adults in order to characterize changes in lower extremity sEMG signals in frail older adults.

Secondary objectives are to explore the correlations between EMG parameters and frailty states and to assess the predictive validity and diagnostic value of EMG parameters for frailty states.

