### Sample size calculation

The sample size calculation was performed using G*Power 3.1.9.7, based on an effect size of 0.433 derived from pilot study data. With a power of 80% and an alpha level of 0.05, the required sample size was calculated to be 67 subjects per group. Anticipating a 10% attrition rate, the sample size was adjusted to 75 subjects per group, resulting in a total of 150 subjects to ensure adequate power for detecting significant differences.

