### Muscles to be tested

Based on the relevant literature and preliminary data analysis, the muscles selected for testing in this study are the rectus femoris, semitendinosus, tibialis anterior, and the medial head of the gastrocnemius in both lower limbs of older adult participants.

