### Statistical analysis

Statistical analysis will be conducted using SPSS 24.0 software, with graphical representations generated through Graph Pad Prism 8. Measurement data will be analyzed by the Kolmogorov-Smirnov test (K-S test), expressed as mean ± standard deviation (x̅ ± s) if they adhere to a normal distribution, with comparisons between groups made using the two independent samples t-test. For non-normally distributed data, results will be described using the median (interquartile range) [M(IQR)], and comparisons between groups will be conducted using the Mann-Whitney U test. Count data will be expressed as frequency (n) and constitutive ratio (%), with comparisons between groups performed using the χ^2^ test or Fisher’s exact test, and rank data comparisons utilizing the Wilcoxon rank-sum test. Effect sizes will be calculated using Cohen’s d value, and the significance level will be set at a two-sided *P *< 0.05.

The intraclass correlation coefficient (ICC) analysis, specifically the ICC(3,k) model, will be used to quantify the consistency and reproducibility of measurements. To assess the reliability of single measurements, the standard error of measurement (SEM) will be calculated using the formula SEM = SD/$\sqrt{n}$, where n represents the number of measurements per participant (i.e., 3). Additionally, the minimum detectable difference (MDD) will be calculated using the formula MDD = SEM × 1.96×$\sqrt{2}$ to determine whether observed differences exceed those expected from measurement error alone, at the 95% confidence level.

Associations between sEMG parameters and frailty status will initially be assessed using Pearson correlation analysis for normally distributed data or Spearman rank correlation analysis for non-normally distributed data. Subsequently, EMG parameters significantly associated with frailty status will be included in binary logistic regression models to further assess their predictive ability for frailty status, controlling for potential confounders such as age and gender. Finally, EMG parameters that prove significant in the logistic regression analysis will be evaluated for their sensitivity, specificity, and cutoff values for diagnosing frailty using receiver operating characteristic (ROC) curves.

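### The plan does not say how left and right leg values enter the group comparison; a pre-specified left-right mean would halve the base-parameter tests and, under stated assumptions, raise power with no extra recruitment

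*Protocol article*

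**What the plan says.** The article's primary objective names four leg muscles, and its list closes with the "medial head of the gastrocnemius muscles in both lower extremities during a 10-meter walk test between frail and non-frail older adults". Under Muscles to be tested, the four muscles are again taken "in both lower limbs of older adult participants". The primary outcomes are RMS, IEMG, AEMG, MPF and MF, together with the symmetry index (SI), activation sequences and contribution rates.

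For normally distributed data the Statistical analysis section has "comparisons between groups made using the two independent samples t-test", with the Mann-Whitney U test otherwise, and "the significance level will be set at a two-sided" 0.05. Under Test program, results are averaged over three walks. The article brings the two legs together only in SI, which contrasts left and right RMS, and in the contribution rate, whose denominator covers all test muscles. For the five base parameters it does not say how a participant's two legs become the value that is compared.

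The sample size is "based on an effect size of 0.433 derived from pilot study data". The muscle, parameter and side behind that figure are not named.

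**The concern.** Eight recording sites and five base parameters give 40 values per participant, and the stated tests compare one value per participant at a time. The literal result is 40 group comparisons in which the left and right versions of the same muscle and parameter are judged separately.

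That fits the design poorly. Frailty is defined by Fried's phenotype as one score for the whole person, and no dominant-leg or one-sided hypothesis is stated. Separate testing leaves the second leg's precision unused and doubles the number of tests. It also invites results where one side differs and the other does not, which the study has no hypothesis to explain. The later steps inherit the problem, because parameters significantly associated with frailty go on to logistic regression and then ROC analysis. Left and right versions of one parameter could both go forward and, to the extent that they correlate, would be collinear.

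Precision matters here because the planned size is smaller than the stated two-sided test needs.

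**Working it through.** **Inputs.** From Sample size calculation: d = 0.433, 80% power, alpha 0.05 (sidedness not stated there), 67 per group, and 75 after 10% attrition. From Statistical analysis: independent-samples t-test, two-sided 0.05. Not in the documents: the left-right correlation rho within groups, and the leg or legs to which 0.433 refers.

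**The plan's own figure.** For n per group, use the noncentral t distribution with 2n − 2 degrees of freedom and noncentrality d·√(n/2). At n = 67 these are 132 and 0.433 × √33.5 = 2.51.
- One-sided 0.05: 80% power needs 67 per group (power 80.2%), and 67/0.9 = 74.4, rounded up to 75. The stated numbers reproduce.
- Two-sided 0.05: 80% power needs 85 per group, and 85/0.9 = 94.4, rounded up to 95. Power at 67 per group is 70.1%; it is 75.0% if all 75 are evaluable.

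The shortfall at 67 per group is therefore 80 − 70.1 = 9.9 points.

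**Effect of averaging the legs.** Assume equal standard deviations and equal effects on both sides, and that 0.433 is a single-leg effect. The mean of two legs has variance σ²(1 + rho)/2, so its standardised effect is d_mean = 0.433/√((1 + rho)/2). For example, rho = 0.5 gives 0.433/√0.75 = 0.500.

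| rho | d_mean | Power, 67 per group | Power, 75 per group | Share of the 9.9 points regained at 67 |
|---|---|---|---|---|
| 0.5 | 0.500 | 81.9% | 86.0% | all |
| 0.7 | 0.470 | 77.0% | 81.5% | 70% |
| 0.8 | 0.456 | 74.6% | 79.3% | 46% |
| 0.9 | 0.444 | 72.3% | 77.1% | 22% |
| 1 | 0.433 | 70.1% | 75.0% | none |

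At 67 per group, 80% power is regained only if rho is about 0.58 or less, and half of the shortfall only if rho is about 0.78 or less. With all 75 per group evaluable, 80% is reached for rho up to about 0.77.

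**Sensitivity to unequal effects.** If one leg's effect is 0.8 of the other's 0.433, the average is 0.433 × 0.9 = 0.390. At rho 0.5, d_mean = 0.390/√0.75 = 0.450 and power is 73.4%. At rho 0.7 it is 68.0%, slightly below the 70.1% for the stronger leg alone.

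**Number of tests.** 4 muscles × 2 sides × 5 parameters = 40; with a left-right mean, 4 × 5 = 20. This does not depend on rho.

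**The case against.** The strongest reply is that silence is not a plan. A t-test on each participant's left-right mean is compatible with the Statistical analysis section, and a fuller protocol or analysis plan may define it. This stands in part: pooling is not ruled out, and side-by-side testing is only the literal reading. But the article does state the averaging over walks, the choice of gait cycles and the formula for SI, so the absence of any rule for the legs in the primary comparison deserves a clear answer.

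A reader might also infer that the two legs will be entered as independent observations, which would inflate the type I error. No passage plans this, and it is not part of the point.

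Second, the protocol makes left-right difference a primary outcome through SI, so side may carry signal, and reporting both legs is legitimate for an objective that sets out to characterise changes. SI is also an incomplete fallback. It is built from RMS only, and it is signed, so group means can cancel if the weaker side varies between participants. These objections stand, and they are why side-specific values should be kept as secondary or descriptive results.

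Third, the power gain depends on quantities that the documents do not give. That also stands and limits the claim.

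**Conclusion.** The point holds as a gap in the definition of the primary comparison with an inexpensive improvement available. The halving of the base-parameter tests from 40 to 20 holds whatever the correlation, taking the literal side-by-side reading as the starting point.

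The gain in two-sided power, from about 70% to between 72% and 82% at 67 per group for rho from 0.9 to 0.5, is conditional. It needs 0.433 to be a single-leg effect, similar effects and standard deviations on both legs, and rho below 1. If the pilot value was already a two-leg mean, nothing is gained.

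A reader might infer that averaging the legs would recover much or all of the lost power. The documents do not support that, because they give neither rho nor the side behind 0.433. Nor does averaging repair the cause of the shortfall: 67 per group matches a one-sided 0.05 test, while the analysis is two-sided. That mismatch needs its own correction. Twenty tests also remain a multiple-testing question.

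**What to change.** State before analysis that, for each muscle, the main analysis value of RMS, IEMG, AEMG, MPF and MF is the participant's mean of left and right, taken after averaging the three walks. Run one group comparison per muscle and parameter. Keep side-specific values as secondary or descriptive results, and leave SI and activation sequence side-specific.

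Estimate the left-right correlation from the pilot data, and state which parameter, muscle and side (or two-leg mean) the 0.433 refers to, so that the actual gain can be given. Restate the sample size and power separately for the two-sided test.

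The cost is analysis wording and a short look at the pilot data, with no added participant or measurement. The downside is that separate comparisons for each leg lose main-analysis status, and SI then covers asymmetry in RMS only.

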## Methods and analysis

### Research design

This is an observational category matching case-control study. The study research will be developed according to the Strengthening the Reporting of Observational Studies in Epidemiology (STROBE) [22] and the Standard Protocol Items: Recommendations for Interventional Trials (SPIRIT) [23] (S1 Appendix).

### Ethics and dissemination

The study will be conducted according to the guidelines of the Declaration of Helsinki and has been approved by the Ethics Committee of Xiamen Cardiovascular Hospital of Xiamen University (Ethical Approval No. [2023] Medical Ethics Science No. 39; approval date: November 8, 2023). Before participation, research assistants will provide a comprehensive explanation of the study’s objectives, methods, potential risks, and benefits, followed by obtaining written informed consent from each participant. Participants will have the right to withdraw at any time without affecting their medical care. All relevant data from the research process will be accurately recorded in the Case Report Forms designed by the research team for subsequent organization and analysis (S2 Appendix).

Access to participant data will be limited to authorized team members only, and all personal identifiers will be removed. Participants will be assigned unique identifiers to ensure confidentiality. The collected data will be securely stored and used exclusively for the purposes defined in the study protocol.

The dissemination of the results will be conducted irrespective of the outcome. Findings will be submitted for publication in peer-reviewed journals and presented at relevant scientific conferences. Summaries of the results will also be made available to participants upon request. All publications and presentations will be based on data that has been fully anonymized to protect participant privacy.

### Study status and timeline

This study is currently ongoing. Participant recruitment began in November 2024 and is expected to continue until June 2025. Data collection has been conducted concurrently since January 2025 and is anticipated to conclude in July 2025. Following the completion of data collection, data analysis will be conducted, with an estimated completion date of October 2025. The results of this study are expected to be available shortly thereafter. The timeline presented herein accurately reflects the status of the study as of the manuscript submission date. The study timeline and assessment schedule are detailed in Fig 1.

**Fig 1 pone.0325356.g001:**
[figure not shown]
SPIRIT schedule of enrolment, assessments, and analysis phases for the observational case-control study on lower limb sEMG.

### Participants

Recruitment for the study will take place from November 2024 to April 2025 using non-randomized convenience sampling. Seventy-five older adults from the inpatient and outpatient departments of the Xiamen Cardiovascular Hospital of Xiamen University in China, who are assessed as frail using the Fried’s frailty phenotype [24], will be selected for the case group. An additional 75 non-frail older adults, matched by age, gender, and cultural background during the same period, will form the control group. All participants will sign an informed consent form (S3 Appendix) and undergo baseline assessments, which include comprehensive socio-demographic and clinical data collection, along with screening using the Fried’s frailty phenotype (S4 Appendix). A panel investigator will review the inclusion and exclusion criteria and assign participants to either the case or control group based on the Fried’s frailty phenotype screening results.

### Selection criteria

#### Inclusion criteria.

(1)Case group1)Older individuals evaluated as frail using the Fried’s frailty phenotype [24], which includes five criteria: (i) Unintentional weight loss: a loss of more than 4.5 kg or more than 5% of body weight over the past year, excluding dieting and exercising. (ii) Slowed walking speed: time taken to walk 4.57 meters, assessed in conjunction with height and gender. (iii) Reduced grip strength: older adults are instructed to measure grip strength twice with their usual hand, and the average of these two measurements is evaluated against gender and body mass index (BMI). (iv) Decreased physical activity: measured using the Minnesota Leisure Time Activity questionnaire, with activity levels less than 383 kcal/week for men (approximately 2.5 hours of walking) and less than 270 kcal/week for women (about 2 hours of walking) indicating a reduction. (v) Self-reported fatigue: assessed using two questions from the Center for Epidemiological Studies-Depression (CES-D). Question 1: ‘I felt that everything I did was an effort during the past week.’ Question 2: ‘I could not get “going” during the past week.’ Scoring for questions 1 and 2 assigns 0 points for less than 1 day, 1 point for 1–2 days, 2 points for 3–4 days, and 3 points for more than 4 days, with a score of 2–3 points on any question indicating significant fatigue. One point is awarded for each criterion met, with a higher score indicating greater frailty. Scores of 3 or more indicate frailty, scores of 1–2 indicate pre-frailty, and a score of 0 indicates no frailty. 2) Age 60 years old and above. 3) Those who can walk independently without assistive devices. 4) Those who possess normal reading, understanding, and expressive abilities to engage in relevant assessments and tests. 5) Those who voluntarily participate in the study and sign the informed consent form.(2)Control group.

The control group will include older adults without frailty, with all other inclusion criteria identical to those of the case group.

### Exclusion criteria: all participants

(1)Complicated with other serious neuromusculoskeletal injuries or diseases.(2)Complicated with severe cardiovascular, cerebrovascular, or psychiatric conditions.(3)Inability to perform the required maneuvers.(4)Allergic to surface electrodes.(5)Complicated with other serious medical illnesses or other reasons for not being able to complete the test.

### Sample size calculation

The sample size calculation was performed using G*Power 3.1.9.7, based on an effect size of 0.433 derived from pilot study data. With a power of 80% and an alpha level of 0.05, the required sample size was calculated to be 67 subjects per group. Anticipating a 10% attrition rate, the sample size was adjusted to 75 subjects per group, resulting in a total of 150 subjects to ensure adequate power for detecting significant differences.

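### The 67 per group matches a one-sided t-test, but the analysis is two-sided, so power is about 70% (75% with no losses), not the stated 80%

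*Protocol article*

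**What the plan says.** The Sample size calculation section reports a G*Power calculation "based on an effect size of 0.433 derived from pilot study data". It continues: "With a power of 80% and an alpha level of 0.05, the required sample size was calculated to be 67 subjects per group". A 10% allowance for attrition then raises the figure to 75 per group, 150 in total. The section names neither the test, nor the effect-size metric, nor whether alpha is one- or two-sided.

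The Statistical analysis section supplies what is missing. For normally distributed measurements it has "comparisons between groups made using the two independent samples t-test", with the Mann-Whitney U test otherwise. It adds "Effect sizes will be calculated using Cohen’s d value", and "the significance level will be set at a two-sided" P < 0.05. The abstract gives 1:1 group sizes.

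**The concern.** A two-group comparison with a standardised effect of 0.433, 80% power and two-sided 0.05 should need more than 80 participants per group, so 67 looks too small. The likely cause is that the sample size was computed for a one-sided test while the analysis is two-sided.

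If so, the protocol's assurance of adequate power fails for the analysis it specifies. A non-significant comparison would be read against a 20% risk of missing the design effect when the real risk is up to 30%.

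**Working it through.** **Inputs**

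- Standardised effect d = 0.433, power 80%, alpha 0.05, 67 per group, attrition 10%, 75 per group recruited: Sample size calculation.
- Independent-samples t-test, two-sided 0.05, Cohen's d as the effect-size metric: Statistical analysis.
- 1:1 group sizes: abstract, Methods.
- Assumption: 0.433 is Cohen's d. No SD is needed, because the effect is already standardised.

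**Formula.** With n per group, df = 2n − 2 and noncentrality λ = d × √(n/2). One-sided power is P(T > t(0.95, df)). Two-sided power is P(|T| > t(0.975, df)). T follows a noncentral t distribution with parameters df and λ.

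**Step 1: reproduce the protocol's figure.** At n = 67, df = 132 and λ = 0.433 × √33.5 = 2.506.

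- One-sided, critical value 1.656: power 80.2%. At n = 66 it is 79.7%. The smallest adequate n is 67, an exact match.
- Attrition: 67/0.9 = 74.4, rounded up to 75. This step is correct.

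**Step 2: apply the planned two-sided test.**

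| n per group | λ | Critical t | Two-sided power |
|---|---|---|---|
| 67 | 2.506 | 1.978 | 70.1% |
| 75 | 2.652 | 1.976 | 75.0% |
| 84 | 2.806 | 1.974 | 79.7% |
| 85 | 2.823 | 1.974 | 80.1% |

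The two-sided requirement is 85 per group. With 10% loss this is 85/0.9 = 94.4, so 95 per group and 190 in total.

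The normal approximation agrees: n = 2 × (1.960 + 0.842)² / 0.433² = 83.7, so 84 two-sided; and 2 × (1.645 + 0.842)² / 0.433² = 66.0, so 66 one-sided.

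**Step 3: what the planned size can detect.** With two-sided 0.05 and 80% power, the smallest detectable d is 0.488 at 67 per group and 0.460 at 75 per group.

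**Step 4: look for another route to 67.**

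| Calculation with 0.433 | One-sided n | Two-sided n |
|---|---|---|
| Independent t-test | 67 | 85 |
| Mann-Whitney, efficiency 3/π (normal data) | 70 | 89 |
| Mann-Whitney, minimum efficiency 0.864 | 78 | 99 |
| Paired t-test, 0.433 as the within-pair effect (pairs) | 35 | 44 |

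Only the one-sided independent t-test returns 67. It does so only for d between about 0.432 and 0.435, a narrow window that contains 0.433. For 67 to be the two-sided answer, d would have to lie between about 0.488 and 0.491.

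**The case against.** **Sidedness is inferred.** The sample size section does not say that the calculation was one-sided, nor that 0.433 is Cohen's d. This stands as a matter of wording. It does not remove the problem: given the Cohen's d reading, the stated inputs with the stated two-sided test give 70% to 75% power however 67 was obtained. The exact match, and the naming of Cohen's d in the analysis section, make the inference strong.

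**The groups are matched, so a paired calculation could apply.** The 44 and 35 pairs above hold only if 0.433 is the within-pair standardised difference. If it is a between-group d, the number of pairs depends on the within-pair correlation r, through a within-pair effect of d/√(2(1 − r)). For 67 pairs to give 80% two-sided power, that effect must be 0.347, which implies r of about 0.22. The protocol gives no such correlation, so this is a hypothetical route. It is also moot, because the plan specifies independent-samples tests.

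**70% is the pessimistic end.** True. Participants are assessed without follow-up, so losses may be small. With no loss at all, power is 75.0%, still below 80%. The extra 8 per group are the protocol's own attrition allowance, not a reserve.

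**There is no single primary test.** The protocol lists several kinds of primary outcome, for four muscles in both legs. The power figures therefore apply only to a parameter whose true d is 0.433, analysed by t-test. This stands, and it is why the corrected text should name that parameter. Under the Mann-Whitney fallback with near-normal data, power would be slightly lower: about 68% at 67 and 73% at 75 per group.

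**The error is mild.** The analysis remains valid and the type I error is unaffected by this point. That limits the consequence to the power claim, but the claim is still wrong as written.

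**Conclusion.** The concern holds. With d = 0.433, the two-sided independent t-test at 0.05 needs 85 per group for 80% power, 18 more than the 67 stated. The planned sizes give 70.1% (67 evaluable) to 75.0% (75, no loss), a shortfall of 5 to 10 percentage points. The type II error at the design effect is 25% to 30% instead of 20%.

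This rests on 0.433 being Cohen's d and on the t-test being the analysis used. That the original calculation was one-sided is a strong inference, not a documented fact. Nothing else in the protocol article resolves the mismatch or justifies a one-sided test.

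**What to change.** Correct the Sample size calculation paragraph and leave the design as it is. Suggested text:

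> For the comparison of [named sEMG parameter, named muscle] between groups by a two-sided independent-samples t-test at the 0.05 level, 67 evaluable participants per group give 70% power to detect Cohen's d = 0.433 (75% with 75 per group). With 67 per group, 80% power is available for d of 0.49 or more.

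The two bracketed items must come from the sponsor's pilot work, since the protocol does not say to which measure 0.433 refers. The analysis should stay two-sided. The protocol gives no reason for a directional hypothesis, and its symmetry index is signed so that either direction is meaningful.

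The cost is one paragraph and a less favourable power statement. No further participants are needed. If the sponsor wishes to keep the 80% claim for d = 0.433, the price is 95 per group (190 in total) with the same 10% allowance, 40 more than planned.
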